### Statistical and Health Economic analyses

Differences in the primary outcome, recurrence of haemorrhoids between the two treatment groups, will be analysed using logistic regression adjusting for sex, age at surgery and history of previous intervention as fixed effect covariates and surgeon as a random effect. This permits the calculation of odds ratios and their confidence intervals for the effect of HAL relative to traditional RBL adjusting for the effects of covariates and the clustering by surgeon. Further detailed analysis of haemorrhoid recurrence will be performed by analysing the length of time to recurrence under a Cox-proportional hazards model adjusting for the same covariates. The secondary outcome of pain, as measured on the visual analogue scale (VAS), with repeated measures will be analysed under a multi-level longitudinal approach adjusting for the same covariates. The secondary outcome of procedural complications elicited during the complications review or from the patient notes at 6 weeks and one year post surgery, will be compared between the two groups at each time point using Poisson regression which accounts for the essentially random nature with which complications arise, although care will be taken to note whether there is any clustering by surgeon. The emphasis of all analyses will be on estimating effect sizes of HAL surgery on recurrence rates and other outcomes in comparison to standard treatment with RBL, and as such appropriate confidence intervals will be reported for all estimates.

We will collect data as part of the trial that will allow us to conduct a full economic evaluation. The main economic analysis will focus on estimating the incremental cost per quality adjusted life year (QALY) of HAL versus RBL over the 12 month follow up period of the trial in: a) patients with new haemorrhoids; and, b) patients with recurrence following RBL. We will also present results in terms of the incremental cost per recurrence avoided.

The time horizon compares to 12 months used in an evaluation of SH versus RBL in patients with grade II haemorrhoids conducted alongside a pilot clinical trial
[26] and 3 years in a modelling study comparing SH and OH
[2]. The former study recommended larger trials and longer follow up. Since it is likely that both surgical complications and recurrence rates will differ at 12 months we will also use decision modelling to extrapolate beyond the trial outcomes. We will draw on and develop as appropriate the model reported in the HTA report
[2]. This model is also being considered for adaptation alongside a model that includes RBL, by those conducting the eTHoS trial (HTA 08/24/02) of stapled haemorrhoidopexy (SH) vs. traditional haemorrhoidectomy (OH). We will liaise with the eTHoS project team to ensure consistency, where appropriate, in our approaches to model adaptation. This will include issues around both model structure and time horizon, as well as parameter values where these are common to both decision problems. This will also avoid unnecessary duplication of workload, particularly in relation to reviewing.

Patients will be asked to complete the EQ-5D instrument at baseline and 1 day, 7 days, 21 days, 6 weeks and 12 months following the treatment. The UK population tariffs will then be used to calculate QALYs for each patient. EQ-5D has been applied in previous studies in this area
[26] and appears to be sensitive to changes in patient outcomes. Pain is likely to be one of the main symptoms in which we might expect the treatments to differ and this is well reflected in the EQ-5D instrument.

In addition, we will explore the relationship between EQ-5D values and specific complications and symptoms, such as relapse, incontinence and pain. We will also consider the relationship between EQ-5D and the combined symptom severity score. These explorations may prove valuable to future modelling studies in this area as there is evidence that previous studies have been hampered by limited utility data. Indeed, a specific recommendation of a recent HTA study was “that further research should include RCTs which collect a generic HRQoL measure such as the EQ-5D or SF-36 at follow-up times close to the procedure and, in the long term, calculate an estimate of preference-based utility. Baseline data from a trial of this kind would also provide a better estimate of HRQoL and utility of patients with symptoms.” (p.88 HTA report
[2])

We will use appropriate statistical techniques to reflect skewness, repeated measures from individual patients and the clustering of the patients, by surgeon and within different centres. Parameter uncertainty will be fully reflected in the estimates by generating a cost effectiveness acceptability curve. We will also consider other forms of sensitivity analysis to reflect further sources of uncertainty.

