**Methods/design:**

The aim of this study is to establish the clinical effectiveness and cost effectiveness of haemorrhoidal artery ligation compared with conventional rubber band ligation in the treatment of people with symptomatic second or third degree (Grade II or Grade III) haemorrhoids.

Design: A multi-centre, parallel group randomised controlled trial.

Outcomes: The primary outcome is patient-reported symptom recurrence twelve months following the intervention. Secondary outcome measures relate to symptoms, complications, health resource use, health related quality of life and cost effectiveness following the intervention.

Participants: 350 patients with grade II or grade III haemorrhoids will be recruited in surgical departments in up to 14 NHS hospitals.

Randomisation: A multi-centre, parallel group randomised controlled trial. Block randomisation by centre will be used, with 175 participants randomised to each group.

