[6-12]. Recurrence varies from 11% to over 50%. This broad range probably reflects the definition of recurrence (patient symptoms or clinical appearance), the grade of haemorrhoids treated (grade I know prolapse; grade II spontaneously reducible prolapse; grade III prolapse requiring manual reduction; and grade IV un-reducible prolapse), the number of treatments and/or the intensity and length of follow up. In most studies, the incidence of recurrence is more than 30% and appears greatest for grade III haemorrhoids. Pain is common for a few hours following RBL and occasionally patients experience pain so severe as to require admission to hospital (around 1%
[3]), bleeding (3-4%, sometimes necessitating further treatment
[10]) and vaso-vagal symptoms (3%
[13]). There have also been rare incidences of blood transfusion
[14,15] and severe pelvic sepsis with a few instances leading death
[13]. Recurrences can be treated by re-banding or by surgical intervention.

Although HAL requires an anaesthetic, evidence suggests a recovery similar to RBL but an effectiveness that approaches the more intensive surgical options. The substantial data concerning effectiveness includes one recent systematic review
[5], three Randomised Control Trials (RCTs)
[16-18], one non-randomised trial
[19] and over 20 case series. A recent overview has been carried out by the National Institute for Health and Clinical Excellence (NICE), which concludes that current evidence shows it to be a safe alternative to OH or SH
[20], this is summarised below.

In terms of efficacy, studies with more than 1 year follow up suggest bleeding, pain on defecation and prolapse (surrogates of recurrent symptoms) in 10%, 9% and 11% of patients respectively

Regarding safety, post-operative haemorrhage requiring intervention (readmission, transfusion, reoperation or correction of coagulopathy) was reported in less than 1.2%, haemorrhoidal thrombosis was seen in less than 3.5% and fissure formation in less than 2.1%

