### Proposed sample size

Assuming the proportion of patients who experience recurrence following RBL is 30% and following HAL is 15%, the sample size required to detect a difference in recurrence rates with 80% power and 5% significance is 121 individuals per group. In order to account for any between-surgeon variation and loss to follow-up, we propose increasing this to 175 per group. This increase is based on the conservative assumption that there will be 14 surgeons in the trial (one per centre) and intra-class correlation (ICC) of 2.5% in keeping with typical ICCs observed by Ukoumunne
[21]. A more likely scenario is that each site will have a minimum of two surgeons, in which case the power to detect this difference is 85%; if there is no between-surgeon variation, the power will be 90%. Because the surgical procedure is well-developed and standardised, intra-class correlation should be virtually zero and the proposed sample size should have closer to 90% power.

The impact of loss to follow up will be minimal for the primary endpoint (haemorrhoidal recurrence at 12 months). Patients who do not complete their 12-month follow-up will have their hospital notes reviewed and their GP will be written to in order to ascertain whether any complications or operative procedures were recorded. The only drop-out expected would be where the patient dies, moves out of the area, or has no traceable patient notes, and we anticipate this would be less than the 5% we have now allowed for in this patient population (a previous study of RBL which used only clinical follow up, reported a 1-year loss to follow up of 10%
[22]).

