Eligible patients who have given written informed consent to participate in the study will undergo baseline assessment immediately before randomisation (Symptom score, EQ-5D, Continence questionnaire). After their procedure, patients will be asked to complete questionnaires one, seven and twenty-one days after surgery (EQ-5D, Pain score). At six weeks, further data will be collected at the routine follow-up clinic visits (Symptom score, EQ-5D, Pain score, Health and social care resource use questionnaire, Complications review interview, Need for further treatment questionnaire). Finally, one year after their procedure, they will be sent questionnaires (Symptom score, EQ-5D, Continence questionnaire, Health and social care resource use questionnaire, Complications review interview, Need for further treatment questionnaire, Recurrence) and be followed up by telephone. We will measure recurrence (the primary outcome) at 12 months.

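### The primary model omits haemorrhoid grade, which the protocol links to recurrence, and centre, by which randomisation is blocked; adding both is a small, nearly free improvement

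*Protocol article*

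**What the plan says.** The section Statistical and Health Economic analyses sets out the primary model as "logistic regression adjusting for sex, age at surgery and history of previous intervention as fixed effect covariates and surgeon as a random effect". It carries the same covariates into the Cox model for time to recurrence and the longitudinal model for pain.

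Other parts of the article bear on that list:

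- **Grade.** Of the banding studies, the Background says that in most of them "the incidence of recurrence is more than 30% and appears greatest for grade III haemorrhoids". The Participants section admits both second and third degree haemorrhoids. Grade appears in none of the models described.
- **Centre.** The Abstract says "Block randomisation by centre will be used". Centre is not a term in the primary model. The health-economic part of the analysis section does recognise clustering both by surgeon and within centres.
- **Surgeon.** Proposed sample size takes one surgeon at each of 14 centres as the conservative case and regards two or more per site as more likely.
- **Timing.** The Outcomes section places "baseline assessment immediately before randomisation (Symptom score, EQ-5D, Continence questionnaire") ahead of the procedure, so age at surgery is settled after allocation.

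**The concern.** The covariate list is stated in the article, so this is not a complaint about detail left to an analysis plan. Grade is the one baseline factor that the protocol itself both connects with recurrence and requires for eligibility, and it is absent. Sex and age are included, although the article links neither to recurrence. If the arms differ by chance in their share of grade III, the planned model cannot correct for it, and adding grade after seeing the data would invite the charge of a data-driven choice.

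An analysis should normally reflect the factor used to restrict the randomisation. Here that is centre, and the model has surgeon instead. The two coincide only with one surgeon per centre, which is not the case the authors expect.

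Age at surgery has no value for a randomised patient who never has the procedure. Age at randomisation exists for everyone.

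**Working it through.** **1. The plan's own figures.** Inputs from Proposed sample size: 30% v 15%, 80% power, 5% significance (taken as two-sided).

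n = [1.96·√(2·0.225·0.775) + 0.8416·√(0.30·0.70 + 0.15·0.85)]² / 0.15² = (1.1575 + 0.4889)² / 0.0225 = 120.5, so 121 per group. This matches "with 80% power and 5% significance is 121 individuals per group".

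At 175 per group without surgeon variation, power is 92.3%, or 90.9% after 5% loss (175 × 0.95 ≈ 166); the article says 90%. With 28 surgeons, there are 350/28 = 12.5 patients each. The design effect at an ICC of 0.025 is 1 + 11.5 × 0.025 = 1.2875, and power is 84.6%; the article says 85%. So the trial is sized on between-surgeon variation.

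**2. Power with and without grade.** The article gives no grade split and no recurrence rate by grade, so both are assumed: grade III share 30% to 70%, grade odds ratio 1.5 to 4. The marginal risks are held at 30% and 15%. Power is Φ(|log OR|/SE − 1.96), with the SE from the logistic information matrix.

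Without grade: OR = (0.15/0.85)/(0.30/0.70) = 0.412. SE = √[1/(175·0.1275) + 1/(175·0.21)] = 0.268. z = 0.887/0.268 = 3.306, power 91.1%.

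With grade, 175 per group:

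| Grade III share | Grade OR 1.5 | 2 | 3 | 4 |
|---|---|---|---|---|
| 30% | 91.2% | 91.6% | 92.3% | 92.9% |
| 50% | 91.3% | 91.6% | 92.2% | 92.8% |
| 70% | 91.2% | 91.4% | 91.9% | 92.2% |

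The squared ratio of z values runs from 1.005 to 1.077, equivalent to about 0.5% to 8% more patients. A simulation of 4,000 trials at a 50% share gave 92.0% v 92.4% (grade OR 2) and 92.1% v 93.1% (grade OR 3). These figures ignore clustering and the other covariates.

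**3. What happens to the standard error.** At a 50% share and grade OR 3, the SE of the log odds ratio rises from 0.268 to 0.275, while the odds ratio moves from 0.412 to 0.394. z goes from 3.306 to 3.381. The gain comes from the conditional odds ratio lying further from 1.

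**4. Chance imbalance.** With 166 per arm and half grade III (assumed), the SD of the between-arm difference in grade III share is √(2·0.25/166) = 5.5 points, so the 95% range is ±10.8 points. If grade III recurs 20 points more often (assumed), the estimated difference moves by up to 10.8 × 0.20 ≈ 2.2 points, about 14% of the 15-point target.

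For scale, the SE of the 30% v 15% difference is √[(0.21 + 0.1275)/166] = 4.5 points, a 95% half-width of 8.8. Grade contributes an SD of 5.5 × 0.20 = 1.1 points, and (1.1/4.5)² is about 6% of that variance.

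**5. Surgeon against centre.** With one surgeon per centre the surgeon effect is the centre effect. With two or more, patients of different surgeons at one site share a centre that the model does not contain.

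**The case against.** The strongest reply is that these are modelling choices and not errors. Randomisation already protects against systematic confounding by grade, the ordinary confidence interval already covers chance imbalance, and the gain is at most about two points of power on assumed inputs. The Background sentence concerns banding studies and says nothing of grade after HAL. Design and analysis also agree on surgeon, which is the unit of clustering in both. All of this stands, and it limits the point to a refinement.

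Several stronger readings are tempting, and the article does not support them:

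- **Grade would sharpen the estimate.** A reader might expect a smaller standard error. In logistic regression it rises slightly, as shown above.
- **Untreated patients are lost.** A literal complete-case fit with age at surgery would drop them. If 5% were dropped on top of 5% loss to follow-up, power would go from 90.9% to 89.5%, and at 15% to 85.9%. But the article does not say they are dropped, names no analysis population and gives no untreated share, and the analysis plan may deal with it. For treated patients the two ages are nearly the same number.
- **Surgeon is confounded with arm.** That needs different operators for the two procedures. The Interventions section has all trial surgeons trained in HAL and all senior staff competent at banding, so the same surgeons may do both.
- **Centre should replace surgeon.** That would remove the clustering on which the sample size rests. If each surgeon works at one site, the surgeon effect also carries much of the centre variation. Ignoring a blocking factor usually makes standard errors conservative.
- **The pain model is flawed without baseline pain.** A randomised comparison of pain after the procedure is valid without it. Adjustment would be optional, and its gain has not been quantified.

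**Conclusion.** The point holds as a modest improvement to a covariate list that the article has already fixed. The list omits grade, which the article itself links to recurrence, and centre, the blocking factor, for which surgeon is not a full substitute in the staffing the authors expect. Age at surgery is a poorer choice than age at randomisation.

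Leaving out grade costs about 0 to 2 points of power, for an assumed grade III share of 30% to 70% and grade odds ratio of 1.5 to 4, together with protection against a chance imbalance worth up to about 2 points on the risk difference under the assumptions in step 4. The benefit of adding centre was not quantified. Nothing here biases the planned comparison or alters the sample size.

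**What to change.** - Add grade (II v III) as a prespecified fixed effect in the primary model and in the Cox and pain models that share its covariates.
- Keep the surgeon random effect and add centre, for example as a random effect with surgeon nested within it. Centre as fixed effects would add 13 parameters for 14 centres against about 166 × (0.30 + 0.15) ≈ 75 expected recurrences, so the random form is more economical.
- Replace age at surgery with age at randomisation, and state how surgeon is assigned for a patient who has no procedure.

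The cost is a change of wording before the data are seen. Grade has to be assessed for eligibility, so the entry form need only record which of the two grades applies; centre and age at randomisation are known at entry. The downside is slight: a few more parameters, and an odds ratio that is conditional on grade and so not identical to the marginal one implied by 30% v 15%.

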### Outcomes

The primary outcome measure is ‘recurrence’, defined as the proportion of patients with recurrent haemorrhoids at 12 months, as derived from a telephone assessment in combination with GP and hospital records.

The trial is a pragmatic design with a dichotomous outcome. As no validated symptom score exists, we have based our definition of recurrence on Shanmugam et al.’s systematic review
[6] definition:

1. Cured or improved: Symptom free or mild residual symptoms but not requiring further treatment at the end of study period; or,

2. Unchanged or worse: No symptom improvement and requiring further intervention or suffered complication or deterioration of symptoms.”

This study will simplify Shanmugam's criteria into the following question, asked at 12 months by a research nurse:

‘At the moment, do you feel your symptoms from your haemorrhoids are:

1. Cured or improved compared with before starting treatment; or,

2. Unchanged or worse compared with before starting treatment?’

Any patient who answers ‘1’ but has required further treatment since the initial procedure will be reclassified as ‘2’, identified via hospital records, their consultant, their GP and patient questioning.

Secondary outcome measures:

1. Symptom score (adapted from Nystrom et al.
[23])

2. Health related quality of life (using the EuroQol-5D “The EuroQoL group”
[24])

3. Continence questionnaire (using the validated Vaizey Incontinence Score
[25])

4. Pain score (using a 10 cm visual analogue scale)

5. Surgical complications

6. Need for further treatment including details

7. Clinical appearance of haemorrhoids at proctoscopy following recurrence

8. Health care costs

9. Cost effectiveness

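### The primary logistic model adjusts for no measure of baseline symptom severity, although a symptom score is taken just before randomisation; adding it would bring a modest gain in power

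*Protocol article*

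**What the plan says.** In the protocol article, Statistical and Health Economic analyses, the primary outcome is analysed by "logistic regression adjusting for sex, age at surgery and history of previous intervention as fixed effect covariates and surgeon as a random effect". The list is stated outright and is not deferred to another document.

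Under Outcomes, eligible consenting patients "will undergo baseline assessment immediately before randomisation (Symptom score, EQ-5D, Continence questionnaire"). The symptom score is repeated at six weeks and one year and is the first-listed secondary outcome. The only analytic use of a symptom score that the article spells out is its relation to EQ-5D, in the economic section.

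The primary outcome rests on a question that a research nurse asks at 12 months. Its favourable answer is "Cured or improved compared with before starting treatment; or"; the other answer is that symptoms are unchanged or worse. A patient who gives the favourable answer but has needed further treatment is counted as a recurrence. The same section notes that there is no validated symptom score.

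The Background says of the banding literature that recurrence exceeds 30% in most studies and looks highest in grade III haemorrhoids.

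**The concern.** By the protocol's own account of the literature, disease severity is related to recurrence. A severity measure is taken before randomisation at no extra cost, and the model that decides the trial leaves it out. Two things are lost. A prognostic baseline covariate in a logistic model adds power to the treatment test. It also corrects the estimate for any chance imbalance in severity, which blocking by centre does not control.

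A second, separate matter is the reference point of the 12-month question. The patient compares the present with a state at least a year old, and knows whether the treatment was a procedure under anaesthetic or a clinic banding. The article has no blinding statement, so that the trial is open in effect is an inference, though a safe one. The measured change in symptom score offers a comparison that needs no such recall.

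**Working it through.** **Inputs (protocol article, Proposed sample size)**
- Recurrence: "Assuming the proportion of patients who experience recurrence following RBL is 30% and following HAL is 15" per cent.
- Base size: "detect a difference in recurrence rates with 80% power and 5% significance is 121 individuals per group".
- Planned size: "In order to account for any between-surgeon variation and loss to follow-up, we propose increasing this to 175 per group".
- Power: "if there is no between-surgeon variation, the power will be 90" per cent.
- Loss to follow-up: "we anticipate this would be less than the 5% we have now allowed for in this patient population".

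**Step 1: reproduce the plan's figures.** Two-sided 5% test of two proportions, pooled variance under the null, no continuity correction:

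n = [1.96·√(2·0.225·0.775) + 0.8416·√(0.30·0.70 + 0.15·0.85)]² / 0.15²
= (1.1575 + 0.4889)² / 0.0225 = 120.5, so 121 per group, as stated.

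With 175 less 5% = 166.25 per arm:

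z = (0.15 − 1.96·√(0.34875/166.25)) / √(0.3375/166.25) = (0.15 − 0.0898)/0.0451 = 1.34, giving power of 90.9% against the stated 90%.

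Both figures reproduce, and this point changes neither.

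**Step 2: what the baseline score would add.** The strength of the score is not in the documents, so it is varied as an assumption. Simulation: 4000 trials per setting, 166 per arm, overall recurrence held at 30% and 15%, a standard normal baseline score, and a Wald test of treatment with and without the score.

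| Assumed OR per SD | Power without | Power with | Mean log OR, without → with | Mean SE, without → with | Log OR/SE, without → with |
|---|---|---|---|---|---|
| 1 (no association) | 92.0% | 92.4% | −0.902 → −0.905 | 0.279 → 0.279 | 3.24 → 3.24 |
| 1.25 | 90.5% | 91.0% | −0.897 → −0.908 | 0.279 → 0.281 | 3.22 → 3.24 |
| 1.5 | 90.3% | 91.3% | −0.891 → −0.920 | 0.278 → 0.283 | 3.20 → 3.25 |
| 2 | 91.2% | 93.2% | −0.902 → −0.979 | 0.279 → 0.292 | 3.24 → 3.36 |
| 2.5 | 90.3% | 93.2% | −0.887 → −1.014 | 0.278 → 0.300 | 3.19 → 3.38 |

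A separate run of 3000 trials per setting gave 91.0% to 91.1% without the score and 92.1%, 92.9%, 93.9% and 95.3% with it, for odds ratios of 1.5, 2, 2.5 and 3. At the top of the range the gain is therefore about 4 points.

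**Step 3: read the result.** The simulation error of a single power figure is √(0.91·0.09/4000) = 0.45 points, and a useless covariate (first row) already shows a difference of 0.4. The half-point at an odds ratio of 1.25 is therefore close to nothing; from 1.5 to 3 the gain is about 1 to 4 points. It arises because the adjusted log odds ratio moves away from zero faster than its standard error grows. The standard error itself rises, so a narrower interval for the odds ratio is not on offer.

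Neither simulation included sex, age, previous intervention or surgeon. The increment over the planned model is therefore not shown exactly, and it would be smaller to the extent that those terms already carry severity.

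**The case against.** **On the covariate.** Randomisation keeps the comparison valid without the score. Previous intervention is already in the model and partly stands for resistant disease. The Background remark concerns grade of prolapse, not the symptom score. The score may also act in opposite directions within this outcome: worse symptoms leave more room to report improvement but plausibly raise the chance of re-treatment. All of this stands. It limits the expected gain without giving a reason to leave out a value already in hand.

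**On recall.** A reader might infer that recall bias runs unchecked into the primary endpoint and that nothing in the plan would reveal it. The documents do not support that.
- Further treatment found through records, consultant, GP or patient overrides a favourable answer, so recall decides only patients without further treatment.
- The symptom score at baseline, six weeks and one year is itself a secondary outcome and needs no long recall. If the two disagreed by arm, that could be seen.
- A concordance or supportive analysis is what an article commonly leaves to the statistical analysis plan.
- No misrecall rates are given. As an illustration only: suppose true failure is 30% in both arms and half of failures are untreated. If 10% of untreated banding failures and 25% of untreated artery-ligation failures recall improvement, the spurious difference is 0.15·(0.25 − 0.10) = 2.3 points. With 5% and 40% it is 0.15·(0.40 − 0.05) = 5.3 points. At 166 per arm the chance of a significant result would rise from 5% to about 7% and 19%. Size and direction rest wholly on the assumed rates.

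Nor is the score a gold standard. The article says no validated score exists, the instrument is an adapted one, and unblinded patients report it too. Counting any fall below baseline as improvement would be debatable.

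**Conclusion.** The point holds for the covariate list. The primary model omits baseline symptom severity although a score is measured immediately before randomisation and the protocol's own literature summary suggests that severity matters. The benefit is modest: about 0.5 to 4 points of power on a base of about 91%, for an assumed odds ratio per SD of 1.25 to 3, plus correction of chance imbalance. The planned sample size and stated power are unaffected.

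Adjustment does not correct recall bias; the two matters are separate. A reader should not conclude that the planned analysis is biased by the omission, or that recall error is shown to distort the endpoint. What remains of the recall question is an optional supportive check.

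**What to change.** **Main change.** Add the baseline symptom score, as a continuous fixed covariate, to sex, age at surgery and previous intervention in the primary logistic model, keeping surgeon as the random effect. State a simple imputation for the few missing baseline scores, made without regard to arm or outcome. Fix this before outcome data are seen by arm. It costs a sentence or two in the analysis plan and no new data. The one thing to explain in the report is that the adjusted odds ratio is conditional on the score, so it may lie further from 1 and have a slightly larger standard error.

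**Optional.** Report by arm, as supportive information only, how the recalled 12-month answer agrees with the measured change in symptom score from baseline to one year. This is most informative in patients without further treatment, because the override settles the rest. If the analysis plan already contains such a comparison, nothing more is needed.

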Data will be collected to establish which patients have further treatment for recurrent symptoms or complications following their initial procedure. This will be achieved at the six week clinic visit following the intervention and by interrogating hospital records, asking the patients’ consultants, writing to patients’ GPs and questioning the patient via telephone interview at 12 months. Due to appointment availability the six week clinic visit may actually vary from four to twelve weeks following the intervention; this window is seen as clinically relevant.

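### Poisson regression for complications rests on their being random, but its model-based intervals need variance equal to the mean, and surgeon clustering is only to be noted

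*Protocol article*

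**What the plan says.** In the protocol article, under Statistical and Health Economic analyses, complications are those "elicited during the complications review or from the patient notes at 6 weeks and one year post surgery". The arms are to be compared separately at these two times by "Poisson regression which accounts for the essentially random nature with which complications arise", with the qualification "although care will be taken to note whether there is any clustering by surgeon". No covariates are named for this model, and the article does not say whether a patient contributes a count or a yes/no.

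The same section gives the primary recurrence model sex, age at surgery and "history of previous intervention as fixed effect covariates and surgeon as a random effect". The Cox and pain analyses are said to use the same covariates.

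Under Methods/design, "the six week clinic visit may actually vary from four to twelve weeks following the intervention", which is put down to appointment availability. The Objectives section lists the question of which procedure has fewer complications among the secondary research questions.

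**The concern.** The reason given for the model is not a sound one. Any statistical model allows for randomness. What Poisson regression adds is a specific assumption: events are independent and, given the covariates, the variance equals the mean. Its usual standard errors depend on that.

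The Background section describes events that can come in chains in one patient: pain severe enough for admission, bleeding that needs further treatment, occasionally transfusion. If these are counted per patient, the variance is likely to exceed the mean and the interval is too narrow. If each patient is scored yes/no, the variance is below the mean and the interval is too wide. Noting surgeon clustering, rather than modelling it as for recurrence, adds an inconsistency within one section.

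At stake is the safety comparison. An interval that is too narrow could support a claimed difference in complications that is not there.

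**Working it through.** **1. The plan's own figure.** The article gives none for complications. Its only design figure, 121 per group for recurrence of 30% against 15% (80% power, 5% significance, taken as two-sided), reproduces: [1.96·√(2·0.225·0.775) + 0.8416·√(0.30·0.70 + 0.15·0.85)]² / 0.15² = 120.5, rounded up to 121. It does not bear on this point.

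**2. Inputs.** From the documents: 175 per group, 14 surgeons (one per centre), a six-week visit at 4 to 12 weeks, and quoted rates of about 1% to 4% per complication type after RBL. Assumed, because the article does not give them: the variance-to-mean ratio φ, mean complications per patient (0.1 and 0.3), the composite any/none rate, and the surgeon standard deviations.

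**3. Counts that cluster within patients.** If variance = φ·mean, the true standard error is √φ times the model's, so the true two-sided error is 2·[1 − Φ(1.96/√φ)].

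| φ (assumed) | True error | Coverage of nominal 95% interval |
|---|---|---|
| 1.1 | 6.2% | 93.8% |
| 1.25 | 8.0% | 92.0% |
| 1.5 | 11.0% | 89.1% |
| 2 | 16.6% | 83.4% |

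A simulation of unadjusted Poisson Wald tests (175 per arm, no true difference, 20,000 runs, gamma-mixed counts with φ = 1 + k·mean) agrees. Pure Poisson data gave 4.7%. With k = 1 the error was 5.6% at mean 0.1 (φ = 1.1) and 8.6% at mean 0.3 (φ = 1.3). With k = 3 it was 8.0% (φ = 1.3) and 14.9% (φ = 1.9).

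**4. Any/none outcome.** The model takes the variance of a log rate as 1/(np); the true value is (1 − p)/(np). With equal rates in both arms the interval is too wide by the factor 1/√(1 − p).

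| Rate p | Factor | Excess width |
|---|---|---|
| 1% | 1.005 | 0.5% |
| 3% | 1.015 | 1.5% |
| 5% | 1.026 | 2.6% |
| 10% | 1.054 | 5.4% |
| 20% | 1.118 | 11.8% |

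These are large-sample results. At 1% only 175 × 0.01 = 1.75 events are expected per arm, and any normal-theory interval is rough.

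**5. Surgeon.** The same simulation was run with 14 surgeons, each treating both arms.
- Surgeon effect shared by the arms (SD 0.5 on the log scale): error 4.4% at mean 0.1 and 5.0% at mean 0.3. There is no inflation, because the effect cancels in the comparison.
- The same, plus a surgeon effect drawn separately for each arm (SD 0.3): error 6.0% and 9.7%.

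**6. Six-week window.** A visit time uniform on 4 to 12 weeks has mean 8 and variance (12 − 4)²/12 = 5.33, so its squared coefficient of variation is 5.33/64 = 0.083. With events accruing evenly, φ = 1 + 0.083·mean: 1.008 at mean 0.1 and 1.025 at mean 0.3. The simulated error was 4.4% and 5.0%. A window that varies equally in both arms therefore does not spoil the interval.

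**The case against.** The strongest reply is that this is a condensed article with a separate analysis plan that is not shown. Robust variance, a dispersion check and the unit of analysis are commonly settled there. The article promises appropriate confidence intervals for all estimates, and nothing in it rules out a robust or overdispersed Poisson model. That stands: the absence of these details is not itself an error. What remains is what the article does state, namely a named model on an unsound reason and a weaker treatment of surgeon than in the primary analysis. The later promise to reflect "repeated measures from individual patients and the clustering of the patients, by surgeon and within different centres" does not clearly close the gap, because it sits within the economic evaluation text.

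A reader might infer that the intervals are wrong whenever complications cluster by surgeon. The documents do not support that. Patients are individually randomised in equal proportion at every centre, and a surgeon effect shared by the arms causes no inflation. Harm needs surgeon-by-treatment variation, or different surgeons for the two arms, and the article does not say who performs each procedure. Some such variation is plausible: the Interventions section treats RBL as a basic skill of all senior staff but requires only more than 5 prior HAL procedures. Against that, the Proposed sample size section expects almost no intra-class correlation. It is also fair to object that a random surgeon intercept, as in the primary model, would not by itself absorb surgeon-by-treatment variation.

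A reader might also infer that the threefold window distorts the whole complications comparison. It concerns the six-week comparison only, and bias would require visit timing to differ by arm, which nothing in the article suggests.

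Finally, at the 1% to 4% quoted per complication type after RBL, the any/none error is negligible and in the conservative direction. That stands too. A composite rate could be higher, but none is given.

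**Conclusion.** The point holds for a secondary outcome; the primary analysis is untouched. The stated reason for Poisson regression does not secure valid intervals, and the direction of the error depends on a choice the article leaves open. For counts with within-patient clustering, the intervals are too narrow, with true error of about 8%, 11% or 17% at φ of 1.25, 1.5 or 2. For any/none data they are too wide, slightly at low rates and by about 12% at 20%.

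The values of φ, the 20% rate and the surgeon standard deviations are all assumptions. The error rates show sensitivity and should not be read as the error to be expected in this trial. The difference in handling surgeon between the two models is real, but its consequence depends on surgeon-by-treatment variation, for which the article has no figure.

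**What to change.** - Drop the appeal to randomness and state whether the outcome is a count per patient or any/none.
- Keep Poisson regression but use robust (sandwich) standard errors, or use negative binomial regression for counts.
- Use the same covariates and surgeon term as the primary model. If surgeon-by-treatment variation is a worry, examine it separately, since the surgeon intercept alone does not cover it.
- Report by arm the number of patients with at least one complication.
- For the six-week comparison only, count events up to a common fixed day where event dates allow, rather than up to the visit. The article does not say that event dates are recorded, so this needs checking. Do not rely on a log-time offset: it assumes a constant event rate, so a patient seen at 12 weeks would be expected to have three times the events of one seen at 4. The events described are largely early, with pain lasting hours and sloughing at 1–2 weeks after RBL.

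The cost is a short change to the analysis text, slightly more analysis work and possibly somewhat wider intervals. Treatment, recruitment and sample size do not change.
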